### Aim 2: Quantitative Analysis Plan

We will summarize implementation outcomes for Support-Moms users and implementers using descriptive statistics. Success in the implementation survey data will be identified qualitatively and by the top tertile of relevant scales (eg, acceptability, feasibility, satisfaction, and appropriateness). We will explore similarities and differences across HCs and districts over time as well as potential associations between implementation outcomes and effectiveness at HCs and district levels. We will summarize all findings and present them through a Delphi process or technique [97], with a final meeting involving key MOH managers and stakeholders. We will describe the ranked implementation strategies selected by app users and key MOH managers and stakeholders after the dissemination process.

### Aim 2: Qualitative Analysis Plan

In-depth interviews will be digitally recorded and transcribed. The first set of exit interviews will be conducted to understand participants’ or stakeholders’ experiences and perspectives of the Support-Moms intervention and clarify the implementation, service, and client outcomes outlined in Table 4. The goal of the CFIR-informed interviews will be to refine and inform implementation strategies for integrating the Support-Moms intervention into routine maternity care. Qualitative analysis will be inductive [98], and categories will be derived from the different study textile participants, HCPs, and MOH manager and stakeholder interviews. These responses will be transcribed into English, if needed, and coded using NVivo (version 13; Lumivero). Data analysis will be jointly performed. The study coordinator and research fellow will double code 5 sampled transcripts from each category and, together with the principal investigator, resolve any coding disagreements to ensure consistency in the codebook. Dyadic analysis will also be performed between pregnant individuals and their social supporters. Categories will then be developed and presented with illustrative quotes from data to explain experiences, challenges with the intervention, and recommendations to improve its implementation into routine maternity care.

### Aim 3: Evaluating the Cost and Cost-Effectiveness of Implementing the Support-Moms Intervention Into Routine Care and Its Implication for Sustainability

The incremental cost and the cost-effectiveness of the Support-Moms intervention or program will be estimated from HCP and health system and societal perspectives to guide the decision makers on continuation, incorporation, integration, sustained use, and routinization—a method that has previously been used in a Ugandan context [99]. We will measure and record the cost of developing and implementing the intervention (program costs), the cost to HCPs from increasing demand for or use of services, and costs to users (intervention participants and their social supporters). The cost of developing and delivering the intervention will be estimated in consultation with the app developers, data from the pilot study, the maintenance team, time and motion studies conducted at representative sites over a 2-week period, as well as administrative records during implementation. The costs of maternity service use to access care will be collected from all aim 1 participants and HCPs at exit; all intervention users and HCPs will provide the cost of care seeking and intervention involvement. We will identify comprehensive tasks required by both users (eg, time used to seek care) and HCPs (eg, training and staff time) and quantify public-sector resource use during the use and provision of the HCP-led service during the 3 years of implementation. Routine and additional public-sector unit costs will be collected from the health management information system [100] and administrative records at the facility and district levels, MOH, and other safe motherhood implementing partners. Direct and indirect costs to intervention users and HCPs because of involvement in the intervention (such as trainings, time used to seek care, and time used by HCPs to enroll users on the app) will be collected from participant exit interviews and administration records. The costs of providing user phones and solar chargers will be explored.

### Cost-Effectiveness Analysis

Cost analysis will include estimating program costs, costs to HCPs, and costs to users as described above. We will also develop a decision tree model to assess the potential impact of economic, clinical, or health outcomes of the Support-Moms intervention against routine care [101,102]. The model will incorporate cost items, relevant clinical probabilities, and case outcomes, allowing a cost-effectiveness evaluation. We will combine the costs and outcomes for each branch of the tree using branch possibilities to simulate the expected costs and outcomes of the intervention and routine care. We will hypothesize service users using routine maternity services or enrolled on the Support-Moms app (per trial arm) as they pass through different health states over time and within acute and chronic health states of 3 key maternal morbidities of sepsis, postpartum hemorrhage, and hypertensive disorders [70,103-105]. Our cost-effectiveness evaluation will account for the outcomes for both the mother and the infant throughout their lifetime at the annual discounting rate of 3% [106]. The clinical and cost outcomes for the infant (eg, low birth weight and stillbirth or intrauterine fetal deaths) will be incorporated in the decision tree. We will use 1-way and probabilistic sensitivity analyses to quantify the confidence level or robustness in this model analysis output in relation to the outputs and the payer’s willingness to pay thresholds [101,107]. We will estimate ICERs in terms of cost per additional HCP-led skilled birth delivery and per death averted. In addition, we will estimate ICERs per disability-adjusted life years averted and quality-adjusted life years (QALYs) gained (QALYs derived from the collected SF-6Dv2 data) as the main summary measures of cost-effectiveness [108] in line with the country’s gross domestic product per capita (GDPpc) [109], to assess the value for money of adopting or providing the Support-Moms app long-term compared to routine care. If ICERs per QALY or per disability-adjusted life years <300% of GDPpc, Support-Moms will be deemed cost-effective, highly cost-effective for ICERs <100% of GDPpc, and not cost-effective otherwise. The decision tree and cost-effectiveness analyses will be programmed in TreeAge (TreeAge Software, LLC).

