## Methods

### Study Overview

We propose to evaluate the effectiveness and implementation of the Support-Moms app into routine care. We hypothesize that Support-Moms will improve maternity service use and reduce the MMR when integrated into routine care. We will test the effectiveness of the Support-Moms intervention in a randomized controlled design (aim 1); evaluate intervention implementation using the implementation outcomes framework by Proctor et al [66], as outlined in Figure 1 (aim 2); and then refine implementation strategies for future scale-up using the CFIR, as outlined in subsequent sections [67]. We will assess the cost and cost-effectiveness of implementing this intervention into routine care and its implication for sustainability (aim 3). These outcomes will serve as indicators of implementation success or necessary preconditions for attaining desired service outcomes for women in rural, resource-limited settings. This will enable us to identify practical, context-specific, and actionable strategies for achieving optimal implementation effectiveness at a low cost. The intervention strategies were developed in our pilot work together with facility HCPs. In the cost-effectiveness analysis, if Support-Moms and standard of care are found to have equivalent effectiveness, we will conduct a cost-minimization analysis where only the cost of Support-Moms per participant will be estimated and reported (no incremental cost-effectiveness ratios [ICERs] will be calculated). This alternative approach would remain informative to the policy makers and stakeholders in maternity service use. Notably, simultaneous assessment is warranted given the (1) strong preliminary evidence, (2) relatively low investment needed for costing, and (3) overall efficiency of our proposed type 1 hybrid effectiveness-implementation trial approach.

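### The aim 3 cost-effectiveness cut-off is valid only for a health gain; under the literal rule a costlier and less effective Support-Moms would be classified as highly cost-effective

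*Protocol article*

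**What the plan says.** The Cost-Effectiveness Analysis section names the two main summary measures: "we will estimate ICERs per disability-adjusted life years averted and quality-adjusted life years (QALYs) gained". It then fixes the verdict: "If ICERs per QALY or per disability-adjusted life years <300% of GDPpc, Support-Moms will be deemed cost-effective, highly cost-effective for ICERs <100% of GDPpc". The second part reads in full "highly cost-effective for ICERs <100% of GDPpc, and not cost-effective otherwise". The closing word makes this a complete three-way classification. It has no lower bound, no condition on the sign of the health effect, no dominance rule and no net-benefit criterion, and no other section adds one.

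The same section plans two further ratios, to which no threshold is attached: "We will estimate ICERs in terms of cost per additional HCP-led skilled birth delivery and per death averted". On uncertainty it says: "We will use 1-way and probabilistic sensitivity analyses to quantify the confidence level or robustness in this model analysis output", judged against the payer's willingness to pay.

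The Study Overview section takes one case out of the rule: "if Support-Moms and standard of care are found to have equivalent effectiveness, we will conduct a cost-minimization analysis", and then "no incremental cost-effectiveness ratios [ICERs] will be calculated". It does not mention a result in which Support-Moms is less effective.

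**The concern.** A ratio of cost difference to health difference loses the signs of its two parts. A negative ratio can mean cheaper and better, or costlier and worse. A positive ratio can mean costlier and better, where a low value is good, or cheaper and worse, where a high value is good. A one-sided cut-off on the ratio handles only some of these cases.

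The wording also joins the two measures with *or*. If cost per QALY and cost per DALY fall on opposite sides of a threshold, the text can be read as letting either one carry the verdict, or as requiring both.

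Cost-effectiveness is one of the three aims. The aim 3 section says that it is meant to guide decision makers on continuation and integration, and the results go to the Ministry of Health. A rule published in advance should give an unambiguous verdict for every result that can occur.

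**Working it through.** The plan states no figure to reproduce here; the check applies its rule to each kind of result.

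**Inputs.** The cut-offs of 100% and 300% of GDP per capita come from the Cost-Effectiveness Analysis section. The article gives no value for GDP per capita (G), so I assume 1000 currency units and also try 500 and 1500. The cost difference dC and health difference dE (QALYs gained or DALYs averted, Support-Moms minus routine care) are illustrative.

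**Formulas.** ICER = dC/dE. Incremental net monetary benefit at threshold λ is NMB = λ·dE − dC, with λ = G or 3G.

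**General result.**
- If dE > 0, then dC/dE < λ is the same as dC < λ·dE, that is NMB > 0. The written rule and net benefit agree.
- If dE < 0, multiplying by dE reverses the inequality: dC/dE < λ is the same as dC > λ·dE, that is NMB < 0. The written rule then passes exactly the results that net benefit fails.
- If dE < 0 and dC > 0, the ICER is negative and so lies below any positive cut-off, while NMB is negative at every positive λ. This needs no assumed value.

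**Numbers at G = 1000.**

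| Result | dC | dE | ICER | Label under the literal rule | NMB at G | NMB at 3G |
|---|---|---|---|---|---|---|
| Costlier, more effective | +50 | +0.1 | 500 | highly cost-effective | +50 | +250 |
| Costlier, slightly more effective | +50 | +0.01 | 5000 | not cost-effective | −40 | −20 |
| Cheaper, more effective | −50 | +0.1 | −500 | highly cost-effective | +150 | +350 |
| Costlier, less effective | +50 | −0.1 | −500 | highly cost-effective | −150 | −350 |
| Cheaper, less effective | −50 | −0.1 | 500 | highly cost-effective | −50 | −250 |
| Cheaper, slightly less effective | −50 | −0.01 | 5000 | not cost-effective | +40 | +20 |

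Example for the fourth row: 1000 × (−0.1) − 50 = −150, and 3000 × (−0.1) − 50 = −350.

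The first three rows, with a health gain, are classified correctly. The last three are not. The third and fourth rows share one ratio and one label although one is the best possible kind of result and the other the worst.

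**Other values of G.**
- Costlier and less effective (+50, −0.1): highly cost-effective throughout. NMB at G is −100 (G = 500) and −200 (G = 1500); at 3G it is −200 and −500.
- Cheaper and less effective (−50, −0.1): at G = 500 the label is cost-effective, with NMB 0 at G and −100 at 3G. At G = 1500 it is highly cost-effective, with NMB −100 and −400.
- Cheaper and slightly less effective (−50, −0.01): not cost-effective throughout, although NMB is +45 and +35 at G = 500, and +35 and +5 at G = 1500.

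**QALY against DALY.** With dC = +50, suppose that one measure showed a gain of 0.1 and the other 0.01. The ratios would be 500 and 5000, which at G = 1000 are highly cost-effective and not cost-effective. The contrast is deliberately wide; any pair of ratios that straddles a threshold raises the same question. The Abstract lists cost per QALY but not per DALY, whereas the Cost-Effectiveness Analysis section calls both main summary measures, so the article does not settle which decides.

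**The case against.** The strongest defence is that the ratios are defined per QALY gained and per DALY averted. A result with health loss has no gain to divide by, so it lies outside the ratio as defined. Reporting such a result as dominated is ordinary practice, and a condensed article may leave it to a fuller economic plan. The authors also do not apply ratios mechanically, since they drop them when effectiveness is equivalent. Decision makers would see the outcome and cost data alongside the verdict.

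Much of this stands. A reader might infer that the authors intend to declare a dominated app highly cost-effective. No sentence says so, and careful analysts would probably not do it.

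A reader might also infer that the probabilistic analysis would count each dominated simulation draw in the app's favour. The article does not say that the cut-off is applied draw by draw, and its reference to willingness-to-pay thresholds is compatible with a net-benefit method. Nor can the share of such draws be worked out from the article's mortality rates and arm size. That calculation gives the chance that the trial's observed death difference points the wrong way, which is a different quantity, and it assumes that the whole health effect follows deaths. The model also includes maternal morbidity, low birth weight and quality-of-life data.

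The defence does not close the gap. If a health loss is outside the rule, the rule gives no verdict for it, and the residual category would have to absorb it by unstated convention. The matter is more than omitted detail, because the article states a closed criterion that fails for part of the range of results. More skilled births would not guarantee a gain in lifetime QALYs, so a loss cannot be excluded beforehand.

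**Conclusion.** The point holds as a defect in a stated decision rule. The cut-off is valid only for a health gain. Read literally, it gives a dominated result the same label as a dominant one and points the wrong way for a cheaper but less effective result. Inferiority is not provided for, and the article leaves open which measure decides if QALYs and DALYs disagree.

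The misclassification of the dominated case rests on no assumed number. The other illustrations depend on the assumed G, dC and dE. How likely a health loss is in this trial cannot be derived from the article, and no probability is claimed.

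This is a minor, low-cost correction to aim 3. The primary analysis of skilled birth and the sample size are unaffected.

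**What to change.** Replace the cut-off sentence with a net-benefit criterion: Support-Moms is cost-effective at a threshold if λ × (QALYs gained or DALYs averted) − incremental cost is above zero, with λ set at 300% of GDP per capita, and highly cost-effective if this also holds at 100%. Alternatively, keep the ICER cut-off, limit it to results with a health gain, and report dominated, dominant and cheaper-but-less-effective results by quadrant.

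Use the same criterion in the probabilistic sensitivity analysis, reporting the probability of positive net benefit at both thresholds. Name in advance whether QALYs or DALYs decide, and report the other as supporting.

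The cost is one or two sentences in the analysis plan, best added before results are known. No new data or modelling is needed, because the same model outputs serve. The stated probability of cost-effectiveness may become less favourable.

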### Ethical Considerations

The ethics approval was obtained from the Mbarara University of Science and Technology Research Ethics Committee (MUST-2022-631) and Uganda National Council for Science and Technology (HS3366ES). Study site administrative permission was obtained from the Mbarara district health officer, Mbarara City Health Officer, Mitoma District health officer, and the director of clinical services at the MOH. We are continually seeking and obtaining written informed consent from all study participants before enrolling in the study. The participants can withdraw from the study at any time. Participant data are anonymized at all times. The study was registered at ClinicalTrials.gov (NTC05940831). The research outcomes from this study will be published in international peer-reviewed journals and presented to the Ugandan MOH as policy briefs and at selected national and international conferences.

We are making firm attempts to adequately explain study purpose, schedule, expectations at the time of enrollment, and data collection and continually updating residence and phone details at each visit to minimize loss to follow-up. We are using appropriate means of contact based on participant preference and information on the best telephone network for the time of the day to telephone or send text messages, with emphasis that participation in this study is voluntary. However, reasons for decline or withdrawal from the study are being sought and documented. Participants are reimbursed for their study visits; a small compensation for their transport worth approximately UGX 20,000 (US $5.50) altogether is given at the end of each of the 2 planned baseline and exit interviews. Participating HCPs are reimbursed with US $5 as compensation for their time after every interview. The estimated time needed for interviews and other study procedures per visit is approximately 1.5 hours.

## Results

This study was funded in September 2023. Ethics approval was obtained in February 2024, and actual data collection started in March 2024. As of January 2025, 75% (618/824) of all projected study participants have consented and been recruited into the study. Participants are expected to be followed up until delivery, and 15% (124/824) of the participants have exited to date. Data analysis for the trial is expected to start as soon as the last participant exits (expected in March 2026). The qualitative interviews will start in April 2025, and data will be analyzed and published as soon as data collection is done. Data collection is expected to be completed by March 2027.

We are currently recruiting at least 60 women or individuals and their social supporters per month. We have registered no loss to follow-up so far.

## Discussion

We are targeting to recruit 824 pregnant women or individuals who have not yet presented for ANC by their second trimester, residing in Mitooma and Mbarara districts, with self-reported access to a cell phone with reception in their home for personal use, and are able to identify at least 2 social supporters living within the study districts. Uganda has approximately 30 million people who access mobile phones (most adult Ugandans), and 71% of users are connected using a basic feature phone [110]. Women or individuals are being identified by CHWs and VHTs, who then notify the study RAs to contact and seek written informed consent before enrollment into the study. Eligible social supporters who own a cell phone for personal use with reliable reception and know the study participant is pregnant be asked to provide consent and will be recruited within the first 2 weeks preceding enrollment of the pregnant women or individuals to ensure an ongoing relationship at the time of their enrollment. Adult HCPs who conduct deliveries within the study sites and MOH facility managers and stakeholders who participate in budgeting, procurements, or funding for facilities are being identified and offered enrollment into the study.

We developed an intervention aimed at improving communication of targeted, health-related information, motivating and mobilizing SS for pregnant women to use maternity services in rural southwestern Uganda (Support-Moms) [36]. Through an iterative approach, we (1) identified preferred key ANC topics from stakeholder interviews with 30 women and 5 HCPs and characterized a preferred messaging intervention; (2) developed content for SMS text and audio messages with 4 medical experts based on identified topics; (3) designed an app prototype through partnership with an mHealth development company (iStreams); and (4) pilot-tested the prototype and sought user experiences and feedback to refine the intervention through 3 different sets of 10 iterative exit interviews, 2 focus group discussions, and 5 cognitive interviews.

We are currently conducting a type 1 hybrid effectiveness-implementation trial [111] to test if this novel patient-centered mHealth-based SS intervention is effective and cost-effective if implemented into routine care from individual and facility perspectives. We will simultaneously assess other implementation, service, and client outcomes per the framework by Proctor et al [66] and refine implementation strategies for future scale-up using the CFIR (individuals, intervention, inner and outer settings, and process). We hypothesize that this intervention will be an effective and cost-effective strategy to improve maternity service use for women in rural Uganda and similar settings. Data collection is underway. Our results will present the functionality of our mHealth intervention, its ability to stimulate and encourage routine health care use, and improve maternal-fetal health outcomes among all rural women, including those with limited education. The results of our work will be usable for other groups designing similar interventions to promote perinatal health in resource-poor settings. Results of this study will also provide requisite data for maternal health policy change and lay the groundwork for evaluation for a regional implementation of the intervention.

Notably, our study will have some strengths. Unlike in many studies, we used conceptual frameworks to characterize and develop patient-centered content and design aimed at making findings more relevant and generalizable to rural communities where the impact of such interventions is likely to be the greatest. This approach is often lacking in mHealth development, most of which is often led by developers and investigators, with limited input from end users [11,14,112]. While many mHealth interventions have been developed in Uganda [113-115], very few have been in the reproductive health field [114,116], and fewer have been evaluated at scale in the public sector [115,117]. Therefore, our study will be among the first ones to test mobile maternal health apps in a randomized controlled trial in Uganda, concurrently assessing effectiveness and other implementation metrics, information that is critical for guiding ultimate use and integration of this intervention in routine care. In this study, we are studying a high-risk population, in which <70% of women deliver with a skilled attendant [15], <58% attend at least 4 ANC visits (of the 8 recommended by the WHO), and thus are likely to benefit from this intervention. We believe that our grounded approach, using appropriate implementation science models and partnering with key regional stakeholders to evaluate an intervention in a rural low-resource setting, will enhance the likelihood of uptake, adoption, and integration into routine care.

We are leveraging existing CHWs, social networks, and resources to encourage uptake, retention, and adoption within a community that largely depends on family and community networks to thrive [42]. This approach is hypothesized to improve pregnancy experiences, partner involvement, support, communication, and mental health during and after pregnancy, ultimately offsetting the downstream cost of avoidable maternal morbidity and mortality [50-53]. We are also building on our pilot, promising preliminary data, and it will provide vital evidence about effectiveness, uptake, and sustained use of this tailored mHealth approach designed to address common individual, family, and community or societal barriers to health care use in Uganda.

We are building on our experience from our previous work done within a typical public health facility setting to recruit and follow up participants. Many people in Uganda move frequently in search of stable work or new settlements, including pregnant individuals [25]. In addition, some change or lose their mobile phones or phones could be inaccessible at times due to network issues. We are using our previous clinical research experience in conducting similar trials to maximize the feasibility of our mHealth intervention and retention in care. SMS distribution is controlled, and women are routinely scheduled for ANC randomly and independently. Consequently, the risk of contamination (eg, discussing and sharing information) at the facility level is minimized. To minimize potential contamination in the community, we are making an effort to clearly explain the study procedures to CHWs or HCPs and intervention women who may learn about different arm allocations through casual conversations, an approach that worked well during our pilot. We have developed and administered a quality control checklist for a few randomly selected control participants so far to assess contamination between arms every 3 months.

